## Methods and analysis

This project is a parallel mixed-methods study of two Canadian provinces, with thematic data integration at the design and interpretation stages. Ontario and BC were chosen as the two provinces of study because they are populous provinces in Canada with large numbers of live births each year, widespread COVID-19 throughout the pandemic, and access to comprehensive administrative health data relevant for the quantitative arm of this study.

This study was funded in late February 2022. The quantitative cohort creation plans and data access requests were finalized in late Fall 2022. Qualitative data collection was piloted in Summer 2022, and preliminary data from a small sample of Ontario participants was collected in Fall 2022. Qualitative data collection in both provinces is currently ongoing. Study completion is anticipated for February 2024.

### Patient partnership

Our team includes multiple individuals who have lived experience of pandemic pregnancy. Three co-investigators with lived experience helped to design the study, secure funding, and determine priorities. They contributed to the design of the interview guide and acted as pilot interview participants for interview refinement. Two additional researchers with lived experience conducted interviews and will participate in analysis.

### Quantitative design and methods

#### Study design

Using a population-based retrospective cohort design, we will assess differences in rates of clinical care and health outcomes for key pregnancy-related outcomes across three birth groups. A cohort study is appropriate given our interests in making inferences about individuals’ health decision-making and examining individual-level social and clinical exposures. This observational design will enable us to examine the real-world effect of the COVID-19 pandemic on pregnancy-related outcomes within entire jurisdictions [56].

#### Data sources

Administrative health data from two provinces will be obtained from ICES in Ontario and PopData in British Columbia. These databases are comprehensive sources of health administrative data for healthcare encounters using provincial health insurance in each province. We will link multiple maternal perinatal care datasets at ICES and PopData BC concerning using unique encoded identifiers (person-level deterministic linkage) (S1 Table).

#### Cohort creation

Our cohort will be defined using an ICES derived cohort (MOMBABY) in Ontario and the BC Perinatal Data Registry, both of which contain medical records for delivering mothers and newborns. S1 Table provides details.

#### Study population

Our cohort for the quantitative portion will be defined by three groups according to the date they gave birth: January 1 to March 31, 2019; January 1 to March 31, 2021; and January 1 to March 31, 2022 (Fig 1). These groups represent gestation before the pandemic, gestation during the pandemic but before widespread vaccine availability, and gestation after widespread vaccine availability. These timeframes reflect an assumption that in the experience of pregnant people in Ontario and BC, the pandemic “started” with the enactment of public health measures in mid-March 2020. While the three-month birthing window excludes large portions of the year, this approach is necessary to construct groups within each time period that have no overlap in gestational periods. Overlapping gestational periods would result in cohort members being exposed to multiple time periods, leading to bias in our results. These groups are standardized by birth month to reflect evidence of seasonality in birth rates and health outcomes [57, 58].

**Fig 1 pone.0288952.g001:**
[figure not shown]
Study population for quantitative portion by birth group.

To be eligible for inclusion in our cohort, the individual must have had a live, in-hospital birth during our timeframes of interest. Stillbirths are excluded due to confounding factors around length of stay and mental health. Additional criteria are that the birthing person and newborn must have a valid ICES Key Number (IKN), delivery and birth date, the birthing person must be of female sex, and have been eligible for the provincial health insurance plans in Ontario or BC for the entirety of their perinatal period.

We will also describe pertinent characteristics of linked newborns to mothers in our cohort within MOMBABY and the BC Perinatal Data Registry. In addition, we will create a separate matched cohort of females using the Registered Persons Database (RPDB) (Ontario) and the Consolidation File (BC) who were not pregnant during our timeframes of interest for Hypothesis 1.2.

#### Outcomes

We will use COVaxON in ICES and COVID-19 Immunization Data in PopData to define our COVID-19 vaccination outcome. Tdap vaccination status will be derived from the Ontario Laboratory Information System (OLIS); Tdap records are not available in PopData. OLIS and the MSP dataset in BC will define gestational diabetes screening outcomes. The Discharge Abstract Data (DAD) will provide data for our postpartum length-of-stay outcome. New onset of depression, anxiety or adjustment disorder will be ascertained using Ontario Health Insurance Plan (OHIP) diagnostic codes from physician billing claims, the DAD, and the Ontario Mental Health Reporting System (OMHRS) in Ontario; the BCPDR and physician billing claims report cases of depression, mood and anxiety. The timeframes of interest for our outcomes are illustrated in Fig 2.

**Fig 2 pone.0288952.g002:**
[figure not shown]
Timeframes of interest for quantitative analyses.

Data from the OHIP claims database and Medical Services Plan (MSP) dataset in BC will provide information about publicly funded perinatal services. The Registered Persons Database (RPDB) in Ontario, the BC Vital Events and Statistics Births dataset, the DAD, and the National Ambulatory Care Reporting System (NACRS) will provide information on baseline characteristics, covariates, and confounders of interest. The Canadian Index of Multiple Deprivation (CIMD) provides data on area-level socioeconomic and ethnocultural markers of marginalization.

Tdap vaccine record: vaccination can occur between 0–40 weeks. Preferentially received between 27–36 weeks.

Covid-19 vaccine record: 2022 birth cohort was eligible for vaccination during gestation. Vaccine could have been received during or after pregnancy.

Gestational diabetes screening: screening could occur between 0–40 weeks. Typically occurs between 24–28 weeks (or 0–13 weeks for people with obesity).

Postpartum length-of-stay: Interval (hours) between delivery time and discharge time.

New onset of depression, anxiety, or adjustment disorder: A) Gestation: Diagnosed between conception date and index event. B) Postpartum: Diagnosed between index event and 6 months postpartum.

#### Sample size

Each year, there are approximately 140,000 live births in Ontario and 42,000 in BC [59]. Our total population of January 1 to March 31 births over the three-year study period is, therefore, approximately 105,000 in Ontario and 31,500 in BC. Given our use of population-based health administrative data sources, we anticipate achieving large sample sizes to detect differences in outcome rates across groups of interest. S2 Table contains sample size calculations, based on anticipated incidence rates. When we report the findings from this study, we will compute post-hoc power calculations to demonstrate the adequacy of our sample in detecting differences. Guidelines for regression suggest assessing no more than 1 potential candidate predictor per 10–20 events [60, 61].

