#### Inferential

The secondary analysis is to test for associations between our outcomes, primary exposure (birth group), and other covariates using multivariable logistic and linear regression. Covariates will be selected based on review of the literature, affirmed by topic and clinical experts. We will utilize logistic regression for our binary outcomes (i.e., vaccination status, gestational diabetes screening, and new onset of depression, anxiety, or adjustment disorder) and linear regression for our continuous outcome (i.e., postpartum length-of-stay). The best-subset approach will be used to identify the subset of covariates that best define the relationship with each outcome. This approach was selected to avoid suppressor effects commonly found with stepwise methods and statistically pre-determined predictors (e.g., *p* < 0.25). The Akaike information criterion (AIC) will be used to evaluate fit of the multivariable logistic regression models; R^2^ will be used to assess goodness of model fit for linear regression. We will verify model assumptions and employ methods such as robust variance estimation to address violations. We will also stratify these models by area-level information on socioeconomic status and ethnocultural composition to examine differences for low-income and racialized sub-groups.

All analyses will be performed using Statistical Analysis Software (SAS), version 9.4 (SAS Institute, Inc., Cary, North Carolina).

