## Strengths and limitations

This study has several strengths. The large administrative datasets offer significant statistical power to investigate changes in health care use, stratified by markers of socioeconomic and ethnocultural status. The cross-provincial nature of our analysis allows the observation of consistency or change based on different healthcare policies, vaccine availability, medical care provision, and COVID-19 burden. The integration with qualitative data offers the potential for explaining observed differences. Our study team incorporates multiple individuals with lived experience of a pandemic pregnancy, and frontline clinicians who cared for pregnant people in both provinces during the pandemic.

This study has some limitations. Relying on administrative data hinders the ability to gather some data points of interest. For example, neither ICES or PopData have patient-level demographic data about race or socioeconomic status. Instead, we will rely on area-level data abstracted from the 2016 Canadian Census, operationalized through the CIMD. The administrative datasets exclude some births, such as those which took place outside of a hospital setting. Qualitative data will be gathered from people who gave birth between May 1, 2020 to Dec 1, 2021, which may introduce some challenges with recall and social desirability bias. However, our co-investigators with lived experience assure us that due to the unique and challenging nature of these decisions, they are able to recall their decision-making very clearly.

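### Post-hoc power, planned to show that the sample was adequate, cannot do so if computed at the observed effect, and the plan names no other effect

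*Protocol article*

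**What the plan says.** The Sample size section of the quantitative methods starts from annual births ("there are approximately 140,000 live births in Ontario and 42,000 in BC") and derives a January–March population over three years of "approximately 105,000 in Ontario and 31,500 in BC". It points to a prospective calculation: "S2 Table contains sample size calculations, based on anticipated incidence rates". It then commits to a further step once results are in hand: "we will compute post-hoc power calculations to demonstrate the adequacy of our sample in detecting differences".

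The text does not define the post-hoc calculation. It does not say whether power will be evaluated at the observed difference or at one set in advance. The contrasts in question are those between birth groups, estimated "using multivariable logistic and linear regression" (Inferential section). The same section adds smaller analyses: "We will also stratify these models by area-level information on socioeconomic status and ethnocultural composition".

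**The concern.** The sentence gives both a method and a purpose, and in the usual meaning of the term the method cannot serve the purpose. Power evaluated at the observed effect is the p-value on another scale. Once p is known, the sample size adds nothing, so the figure cannot say whether the sample size was sufficient.

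Interpretation is what is at stake. Several hypotheses predict a change between birth groups, so finding no material change would be a real answer, and one to be set beside the qualitative findings. A low observed power would invite readers to put such a result down to an inadequate sample, even where the confidence interval excludes any change of interest. Equally, a significant result at p = 0.03 would appear to come from an inadequate sample when the cohort is an entire province's births.

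**Working it through.** **Inputs.** Annual births of 140,000 (Ontario) and 42,000 (BC) and three birth groups of three months each come from the protocol article. The text shown does not give the significance level, target power, base rates or differences; S2 Table is not shown. Assumed for illustration: two-sided 5%, 80% power, base rates of 10% to 50%, two equal groups, no covariate adjustment.

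**1. The plan's own figure.** 140,000 / 4 × 3 = 105,000 and 42,000 / 4 × 3 = 31,500. Both agree with the plan. Per birth group: 105,000 / 3 = 35,000 in Ontario and 31,500 / 3 = 10,500 in BC.

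**2. Power at the observed effect.** For a normal-theory test with two-sided p-value p, let z_obs be the 1 − p/2 quantile of the standard normal. Then

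observed power = Φ(z_obs − 1.96) + Φ(−z_obs − 1.96).

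Only p enters:

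- p = 0.001: 90.8%
- p = 0.005: z_obs = 2.81, Φ(0.85) ≈ 80%
- p = 0.01: 73.1%
- p = 0.05: 50.0%
- p = 0.10: 37.6%
- p = 0.20: 24.9%
- p = 0.50: 10.4%

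**3. Sample size drops out.** Take a base rate of 10% and find the second rate that gives p = 0.30 at each group size. The standard error is the difference divided by 1.036, and the 95% interval is the difference ± 1.96 standard errors.

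- 35,000 per group: second rate 10.236%, difference 0.236 points, interval −0.21 to 0.68, observed power 17.8%
- 10,500 per group: second rate 10.433%, difference 0.433 points, interval −0.39 to 1.25, observed power 17.8%
- 2,000 per group: second rate 11.005%, difference 1.005 points, interval −0.90 to 2.91, observed power 17.8%

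The first interval rules out an increase of 1 point and the third does not come close to doing so, yet the observed power is the same. At p = 0.05 it is likewise 50.0% at all three sizes.

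**4. What changes when the difference is fixed beforehand.** Power for a rise from 10% to 11% is 99.1% at 35,000 per group and 65.7% at 10,500, so it now responds to sample size. The smallest increase detectable with 80% power is approximately 2.80 × √(2p(1 − p)/n), where p is here the base rate. For Ontario at 10%: 2.80 × √(0.18/35,000) = 0.64 points. Inverting the two-proportion power function, which also allows for the variance at the second rate, gives for base rates of 10%, 30% and 50%:

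- Ontario, 35,000 per group: 0.64, 0.97 and 1.06 points
- BC, 10,500 per group: 1.19, 1.79 and 1.93 points

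**The case against.** The best counter-argument is that the article never says observed rates will be used. The sentence follows directly on a reference to anticipated rates in S2 Table, and power recomputed at the achieved sample size for the S2 Table differences could also be called post-hoc. That calculation would be informative. This stands as a limit on the finding: a reader might infer that the plan certainly commits to restating p-values, and the text does not go that far. It leaves the calculation undefined, under a term whose usual meaning is the uninformative version.

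It can also be said that no hypothesis is accepted or dismissed on the post-hoc power, that the quantitative analysis is primarily descriptive, that the sample is fixed by the population, and that nothing prevents authors from reporting confidence intervals. All of this stands and limits the consequence.

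Three stronger readings are not supported:

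- That every significant result would look adequately powered. Observed power is only 50% at p = 0.05 and 73% at p = 0.01.
- That null results are likely in BC or in the stratified models. The text gives neither expected effects nor stratum sizes.
- That the Strengths and limitations section repeats the error when it says "The large administrative datasets offer significant statistical power to investigate changes in health care use". That is a prospective statement about cohort size, and the detectable differences above are consistent with it.

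**Conclusion.** The point holds in a limited form. As written, the sentence promises evidence of adequacy from a calculation that, in its usual sense, cannot supply it, and it names no externally fixed difference that would rescue it. At the observed effect, non-significant contrasts would all fall below about 50% and significant ones with p from about 0.005 to 0.05 would fall short of 80%, at any sample size. These percentages assume a two-sided 5% normal-theory test; the detectable differences also rest on the assumed base rates, 80% power and no covariate adjustment.

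A reader might infer that the study is underpowered or that its conclusions are compromised. The documents support neither: a prospective calculation exists, the cohorts are large, and no stated decision depends on the post-hoc figure. The harm is confined to how results, especially null ones, might be read.

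**What to change.** Delete the post-hoc power sentence. Rest the adequacy of the sample on the prospective calculations in S2 Table, and show precision through 95% confidence intervals for the birth-group differences, including those in the stratified models.

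If a power statement is still wanted at reporting, define it in one clause: power, or the smallest detectable difference, at the achieved sample size for differences fixed before the results are seen, for example those in S2 Table. If that is what was meant all along, the same clause settles it.

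The cost is a change of wording. No new data or analyses are needed. If S2 Table does not already contain suitable differences, the team would have to agree them before seeing results, but only if it chooses to keep a power statement.

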### Quantitative analyses

#### Descriptive

The primary goal of the quantitative analysis is to describe and compare rates of our outcomes across birth groups to help explain the qualitative findings. Pregnancy-related factors will be reported using measures of general frequency (i.e., counts and proportions), central tendency (i.e., means and medians), and dispersion (i.e., standard derivations and interquartile range). We will examine maternal age, rurality, CIMD measures (i.e., ethnocultural composition, economic dependency, and residential instability), medical practice characteristics of the mother’s perinatal care provider, parity, mental health history (e.g., previous diagnoses or emergency department visits for mental health), the use of assistive fertility, delivery characteristics (e.g., gestation length and delivery type), and newborn outcomes (e.g., infant birth weight and neonatal intensive care unit admission). These factors were identified *a priori* based on a review of the literature and consultations with theme group experts.

Data will be examined for completeness, the presence of outliers, and the nature of the variable distribution for continuous variables (e.g., skew). We will report the completeness range for each exposure variable. Cases with missing data will be deleted within each analysis. Where data are incomplete for key variables, we will consider using multiple imputation.

#### Inferential

The secondary analysis is to test for associations between our outcomes, primary exposure (birth group), and other covariates using multivariable logistic and linear regression. Covariates will be selected based on review of the literature, affirmed by topic and clinical experts. We will utilize logistic regression for our binary outcomes (i.e., vaccination status, gestational diabetes screening, and new onset of depression, anxiety, or adjustment disorder) and linear regression for our continuous outcome (i.e., postpartum length-of-stay). The best-subset approach will be used to identify the subset of covariates that best define the relationship with each outcome. This approach was selected to avoid suppressor effects commonly found with stepwise methods and statistically pre-determined predictors (e.g., *p* < 0.25). The Akaike information criterion (AIC) will be used to evaluate fit of the multivariable logistic regression models; R^2^ will be used to assess goodness of model fit for linear regression. We will verify model assumptions and employ methods such as robust variance estimation to address violations. We will also stratify these models by area-level information on socioeconomic status and ethnocultural composition to examine differences for low-income and racialized sub-groups.

All analyses will be performed using Statistical Analysis Software (SAS), version 9.4 (SAS Institute, Inc., Cary, North Carolina).

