### Theme 3: Mental health and social support

Untreated antenatal depression and anxiety are associated with pre-term birth, low birth weight, and increased risk of infant hospitalization and death within the first year of life [48, 49]. A systematic review and meta-analysis of global data indicate high rates of prenatal depression (30.5%) and anxiety (25.6%) during the COVID-19 pandemic [50]. Pregnant people in Canada may experience even higher rates of depression and anxiety [51], perhaps in response to concerns about threats of COVID-19 to themselves or their fetus, insufficient prenatal care, strained relationships, and social isolation [52]. Mental health concerns may be greater for those who experienced extra stress or safety fears due to income disruptions, difficulties balancing childcare and work responsibilities, are single parents, or had difficulty obtaining childcare [11, 53, 54]. The stress and anxiety experienced during the pandemic may have contributed to lower birth weights, younger gestational age at birth, and other birth-related issues [42, 52]. So far, there are little data about how perinatal mental health diagnosis rates have changed throughout the pandemic. We do not know whether any observed changes in mental healthcare use reflect barriers to accessing care. We do not know how pregnant people experienced their feelings of depression and anxiety, and how they chose to cope with these experiences.

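### Fit-based best-subset selection is a poor way to choose covariates for the secondary birth-group regressions, and unpenalised R² cannot set the size of the length-of-stay model

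*Protocol article*

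**What the plan says.** The article ranks its quantitative analyses. The Descriptive section says: "The primary goal of the quantitative analysis is to describe and compare rates of our outcomes across birth groups to help explain the qualitative findings". The Inferential section says: "The secondary analysis is to test for associations between our outcomes, primary exposure (birth group), and other covariates using multivariable logistic and linear regression". Hypotheses 1.1 (Tdap), 2.1 (gestational diabetes screening), 2.2 (length of stay) and 3.1 (new mental health diagnosis) each predict a direction of difference between birth groups. Each theme also asks a second question: which factors go with the outcome.

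Covariates are chosen in two steps. First: "Covariates will be selected based on review of the literature, affirmed by topic and clinical experts". Then: "The best-subset approach will be used to identify the subset of covariates that best define the relationship with each outcome". The reason given is: "This approach was selected to avoid suppressor effects commonly found with stepwise methods and statistically pre-determined predictors". AIC is to evaluate the fit of the logistic models. For length of stay, R² "will be used to assess goodness of model fit for linear regression". No other criterion is named, and control of confounding is not among the reasons.

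The only list of factors in the article stands under Descriptive. It includes "delivery characteristics (e.g., gestation length and delivery type), and newborn outcomes (e.g., infant birth weight and neonatal intensive care unit admission".

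**The concern.** Two questions share one model-building rule. A contrast between birth groups needs the covariates that confound it, fixed in advance. A search for the best-fitting subset looks for whatever goes with the outcome and takes no account of timing or causal role. Three things follow.

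- The adjusted birth-group coefficient depends on what the search keeps, and standard errors computed as if the model had been fixed in advance are too optimistic.
- For the linear model, the one measure named cannot choose between subsets of different size.
- Variables recorded at or after delivery can predict an outcome strongly without being confounders. They may be consequences of the pandemic period, of the outcome, or of both. Adjusting for them can remove or distort part of the difference that the hypotheses are about.

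**Working it through.** **1. The plan's own figures.** Births per year × 3/12 × 3 groups: Ontario 140,000 × 0.25 × 3 = 105,000; BC 42,000 × 0.25 × 3 = 31,500. Both match Sample size. Per birth group this is 35,000 and 10,500.

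**2. What AIC does.** AIC keeps a one-parameter term when its likelihood-ratio chi-square exceeds 2, and P(chi-square, 1 df, > 2) = 0.157. The article rejects screening at p < 0.25, but AIC filters on the same thing, association with the outcome, at p < 0.157.

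**3. What R² does.** R² = 1 − RSS/TSS, and RSS cannot rise when a term is added, so the largest model always has the highest R². In 200 simulated best-subset runs with five candidates, only one of them real, the full model won 200 times. R² can rank subsets of equal size. Adjusted R² = 1 − (1 − R²)(n − 1)/(n − k), with k parameters, can fall, so it can choose size.

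**4. Timing, from the outcome definitions beside Fig 2.** Gestational diabetes screening typically falls at 24–28 weeks, Tdap preferably at 27–36 weeks, and an antenatal diagnosis before the index event. Delivery type, birth weight and NICU admission come later. Length of stay starts at delivery and the postpartum diagnosis window runs to six months, so there the same variables can precede the outcome and act as mediators. Theme 3 gives a reason for care: "Untreated antenatal depression and anxiety are associated with pre-term birth, low birth weight, and increased risk of infant hospitalization". It also suggests that pandemic stress may have affected birth weight and gestational age. Theme 2 links inadequate prenatal care to preterm birth, low birth weight and NICU admission.

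**5. Size for length of stay, on assumed inputs only.** Two groups; direct birth-group effect −4 h; delivery type +22 h; NICU +10 h, with NICU admission 10 points more frequent after that delivery type; residual SD 20 h. For a shift s in delivery type between groups:

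total effect = −4 + 22s + 10 × 0.10 × s = −4 + 23s

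Adjusting for both variables returns the direct effect, −4 h. The gap is therefore 23s: 0, 0.23, 0.46 and 1.15 h at 0, 1, 2 and 5 points. One simulated dataset per row, birth group forced in:

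| N | Shift (points) | True total (h) | AIC-selected (h) | Age and parity only (h) |
|---|---|---|---|---|
| 70,000 | 0 | −4.00 | −4.11 | −4.05 |
| 70,000 | 1 | −3.77 | −4.10 | −4.09 |
| 70,000 | 2 | −3.54 | −4.17 | −3.72 |
| 70,000 | 5 | −2.85 | −4.15 | −3.12 |
| 21,000 | 0 | −4.00 | −3.79 | −3.84 |
| 21,000 | 1 | −3.77 | −4.06 | −4.06 |
| 21,000 | 2 | −3.54 | −4.49 | −4.02 |
| 21,000 | 5 | −2.85 | −3.55 | −2.52 |

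AIC kept both delivery and NICU variables in all eight datasets. The standard error is roughly 2 × 20/√70,000 = 0.15 h and 2 × 20/√21,000 = 0.28 h, so single rows are noisy; 23s is the cleaner figure. For scale, the difference detectable with 35,000 per group (assumed two-sided 5%, 80% power) is 2.80 × SD × √(2/35,000): 0.42 h at SD 20 h and 0.51 h at SD 24 h.

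**6. Is pruning needed?** The Descriptive list holds about 13 factors, counting three CIMD dimensions. At the stricter guide of 20 events per predictor, an assumed 1% incidence gives 1,050/20 = 52 predictors in Ontario and 315/20 = 15 in BC. An assumed 10% gives 525 and 157. Stratified models and multi-level factors leave less room, but the unstratified models do not need pruning.

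**The case against.** Several stronger readings are tempting, and the text does not support them.

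- *R² is the selector, so length of stay always gets the full model.* The article calls R² a goodness-of-fit measure and does not name it as the selection rule. Used to rank equal-size subsets, or in adjusted form, it would work.
- *Birth group could be dropped.* The article separates the exposure from the other covariates and selects among covariates. The natural reading keeps birth group in, though it does not say so.
- *NICU admission and birth weight will be adjusted for.* They are listed under Descriptive. Both lists are said to rest on literature and experts, and no other list appears, so they may be candidates; this is inference. The expert step may remove them.
- *The article says that preterm birth follows antenatal depression.* It reports an association.

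The status of the analysis also counts. Comparing rates is the primary goal and regression is secondary. Hypotheses 1.2 and 1.3 do not have birth group as exposure, and selection is a fair tool for the associated-factors question. At these sample sizes AIC would rarely drop a strong confounder, and keeping a noise covariate does not bias the coefficient. Adjusting length of stay for delivery type can be defended as case-mix control. If a later event depended on the outcome alone, adjusting for it would leave the birth-group odds ratio unchanged; it must also depend on birth group.

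What is left is a stated method, not an omitted detail: covariates for an exposure contrast are pruned, outcome by outcome, on fit.

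**Conclusion.** The concern holds in a limited form. Best-subset selection on fit does not suit the birth-group contrast, ordinary intervals take no account of it, and unpenalised R² cannot decide how large the linear model should be.

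Distortion from delivery and newborn variables is a conditional risk. They must be candidates, be retained, and differ between birth groups. The article establishes none of the three, although its background sections make the last plausible. A reader might infer that the adjusted birth-group effects will be wrong, but the documents do not go that far. The 0.46 h and 1.15 h figures rest wholly on assumed effects, would change sign if the shift went the other way, and are zero without a shift.

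This should be fixed before the models are run. It does not touch the primary descriptive comparison.

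**What to change.** Separate the two questions in Inferential.

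1. *Birth-group contrast.* Drop best-subset selection. Fit one prespecified model per outcome, the same in both provinces where data allow (Tdap is Ontario only). Force birth group in and add listed factors that precede the outcome and are not consequences of the pandemic period: for example maternal age, parity, rurality, CIMD, fertility assistance and prior mental health history. Provider characteristics need an explicit decision, because Theme 2 describes pandemic changes in how care was delivered.
2. *Delivery and newborn variables.* Keep them out of that model. Show delivery-adjusted length of stay or postpartum diagnosis only as a second model, labelled as adjusted for possible mediators.
3. *Associated factors.* Selection may stay, with the candidate list stated per outcome and a penalised criterion throughout (AIC, or adjusted R² for the linear model). Report it as exploratory.

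The cost is a change of wording, one extra model per outcome and slightly lower apparent fit. No new data are needed.
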